### Hypotheses

We expect blunted CORT and OXT stress responses in adolescents with MDD (with or without comorbid anxiety) relative to healthy controls, whereas baseline levels of these hormones are not expected to differ systematically across groups. For rsFC, we hypothesize time (pre- vs. post-stress) × group (MDD, COM, HC) interactions within fronto-limbic circuits, with greater alterations in adolescents with depressive disorders compared to healthy controls. Exploratorily, we expect that youth with MDD and comorbid anxiety will show more pronounced endocrine blunting and stronger fronto-limbic rsFC alterations than those with MDD alone. Finally, we hypothesize that stress-induced fronto-limbic rsFC changes will be significantly associated with endocrine reactivity (CORT, OXT, sAA), reflecting shared neuroendocrine mechanisms of stress adaptation.

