The second primary outcome is hormonal reactivity. We hypothesize that stress exposure will elicit group differences in OXT, CORT and sAA. Raw hormonal values will be square-root transformed to reduce skewness [93]. Reactivity will be quantified using area under the curve (AUC) [94] with respect to increase (AUC_i_) and ground (AUC_g_), as well as delta scores reflecting change from baseline to peak, peak to recovery, and recovery magnitude [95–97]. Repeated-measures ANOVAs will examine the interaction between time (baseline, peak, recovery; within-subject factor) and group (between-subject factor), controlling for sex, age, and pubertal status. False Discovery Rate (FDR) correction will be applied across hormonal outcomes and indices. Subjective stress ratings assessed with VAS will be analysed in parallel, using repeated-measures ANOVAs with the same model structure.

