#### Secondary outcomes

Structural MRI measures will be derived from T1- and T2-weighted images to calculate cortical thickness, surface area, and subcortical volumes. Group comparisons will be conducted using ANCOVAs, controlling for sex, age, and pubertal status, with FDR correction applied across regions.

DTI data will be preprocessed with QSIPrep [98] for denoising, motion and distortion correction, followed by whole-brain tractography and structural connectome reconstruction as outlined in recent protocols [99]. Cortical parcellation will be based on the Brainnetome atlas, and structural connectivity matrices will be derived from streamline counts and weighted by fractional anisotropy. Graph-theoretical measures (e.g., node strength) will be extracted using the Brain Connectivity Toolbox. Between-group differences will be tested using ANCOVAs including sex, age or pubertal status, and medication status (yes/no) as covariates.

Task-based fMRI will be analysed using GLMs to assess BOLD activation during the stress induction task. At the first level, subject-specific GLMs will be estimated, and at the second level, group differences will be examined using ANOVAs. The primary contrast will compare stress versus baseline, with sex, age or pubertal status, and medication status (yes/no) included as covariates.

Exploratory analyses will include depressive and anxiety symptomatology scores as covariates in rsFC, sMRI, and hormonal models to test whether associations remain robust after accounting for clinical variation. Sex assigned at birth will be recorded, and exploratory analyses will examine group × sex interactions. When appropriate, non-parametric tests (e.g., Mann–Whitney U-tests) will be applied in case of non-normal distributions. Relationships between VAS ratings and hormone levels (OXT, CORT, sAA) will be assessed using bivariate correlations. Multiple regression models will also be applied to assess associations between hormonal systems. In the first model, CORT increase will be the dependent variable, with OXT increase, baseline CORT, and group as predictors. In the second model, CORT recovery will be the dependent variable, with OXT and CORT increase as predictors.

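### The second hormone regression omits group, which leaves its oxytocin coefficient open to confounding, and on the natural reading its outcome and CORT-increase predictor share the peak value

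*Protocol article*

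**What the plan says.** Under Secondary outcomes, the protocol article announces two regressions with this purpose: "Multiple regression models will also be applied to assess associations between hormonal systems". It lists the predictors of each. The first: "In the first model, CORT increase will be the dependent variable, with OXT increase, baseline CORT, and group as predictors". The second: "In the second model, CORT recovery will be the dependent variable, with OXT and CORT increase as predictors". Group and baseline CORT are thus in the first model and absent from the second, and no reason is given. I read OXT in the second model as OXT increase.

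The indices are introduced under Primary outcomes as "delta scores reflecting change from baseline to peak, peak to recovery, and recovery magnitude". The article does not say which of these is the CORT recovery of the second regression.

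The Hypotheses section says: "We expect blunted CORT and OXT stress responses in adolescents with MDD (with or without comorbid anxiety) relative to healthy controls". It adds that "baseline levels of these hormones are not expected to differ systematically across groups".

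For subjective stress, Secondary outcomes says: "Relationships between VAS ratings and hormone levels (OXT, CORT, sAA) will be assessed using bivariate correlations".

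**The concern.** There are two separate problems, and they affect different coefficients.

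**Omitted group (OXT coefficient).** If the clinical groups have lower OXT and altered CORT responses, as the protocol expects, group is a possible common cause of predictor and outcome. Pooling 30 controls with 60 patients without a group term can then produce an OXT–CORT recovery association that exists within no group. The introduction describes conflicting evidence on whether OXT goes with CORT release and recovery, so this coefficient is likely to be read as evidence on that question.

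**Shared peak (CORT-increase coefficient).** If increase is peak minus baseline and recovery is peak minus recovery value, the same peak measurement, with its assay error, enters both sides of the equation. An association then follows from the arithmetic alone.

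The predictors are written out in the article, so this is a stated specification and not a detail left to an analysis plan.

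**Working it through.** The article gives no figure for these regressions, so there is none to reproduce.

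**Inputs.** From the article: 30 per group, two-sided alpha 0.05, predictors as listed, both clinical groups blunted in OXT and CORT, no baseline difference. Assumed, because the article gives no values: group shifts of 0 to 0.8 SD, and correlations among baseline (B), peak (P) and recovery value (R).

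**1. Shared peak.** With equal variances,

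corr(P−B, P−R) = (1 − r_PR − r_BP + r_BR) / √[(2 − 2r_BP)(2 − 2r_PR)].

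- All correlations equal to ρ: (1 − ρ) / (2 − 2ρ) = 0.50 for any ρ.
- r_BP = 0.7, r_PR = 0.8, r_BR = 0.6: 0.1 / √(0.6 × 0.4) = 0.20.
- r_BP = 0.4, r_PR = 0.4, r_BR = 0.7: 0.9 / 1.2 = 0.75.

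In 4,000 simulated data sets of 90 with equal correlations and no recovery effect, the CORT-increase slope averaged about 0.50 and was significant in about 99.9%. Adding group left the slope at about 0.50, significant in at least 99.8%.

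The result depends on the index. If recovery is R−B, the baseline is shared and the correlation is again 0.50 under equal correlations. If recovery is the level R itself, the slope is 0.00 with about 5% significant.

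**2. Omitted group.** Write δP and δR for the clinical-group shifts in peak and recovery level. Within groups the slope of P−R on P−B is σ²(1−ρ) / 2σ²(1−ρ) = 0.5. The group shift in recovery left after adjusting for CORT increase is therefore

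c = (δP − δR) − 0.5δP = 0.5δP − δR.

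OXT picks up c only if OXT also differs by group. Simulated results with no true OXT effect (ρ = 0.5, 4,000 replicates, shifts in SD):

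| OXT, δP, δR | c | OXT slope, no group | False positives, no group | False positives, with group |
|---|---|---|---|---|
| 0, 0, 0 | 0 | −0.003 | 5.0% | 5.0% |
| −0.5, −0.5, 0 | −0.25 | +0.025 | 6.0% | 5.3% |
| −0.8, −0.8, 0 | −0.40 | +0.057 | 10.3% | 5.3% |
| −0.5, −0.5, −0.5 | +0.25 | −0.024 | 5.0% | 4.7% |
| −0.8, −0.8, −0.8 | +0.40 | −0.055 | 9.2% | 5.4% |
| −0.8, −0.5, +0.3 | −0.55 | +0.083 | 14.4% | 5.3% |
| −0.8, −0.8, −0.4 | 0 | −0.002 | 5.4% | 5.1% |
| −0.8, 0, 0 | 0 | −0.002 | 4.6% | 5.2% |

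The sign of the bias follows c, and the bias vanishes when δR is half of δP or when group affects OXT only. The first row contains the shared peak and no group effect: the OXT test keeps its 5%.

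**3. Level model.** Regressing R on OXT, P, B and group gave OXT false-positive rates of 4.6% to 5.6%. Without group, the same model reached 12.7% and 13.0% in the −0.8, −0.8, −0.8 and −0.8, −0.5, +0.3 scenarios, so switching to levels does not replace the group term.

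**4. VAS–hormone correlations.** If both variables are shifted by d SD in the clinical two-thirds, with no within-group association, pooled r = (2/9)d² / [1 + (2/9)d²]. For d = 0.5 this is 0.0556 / 1.0556 = 0.05; for d = 1.0 it is 0.2222 / 1.2222 = 0.18. Simulated false-positive rates were about 8% and 42%.

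**The case against.** **The outcome is not defined as the peak-to-recovery change.** This stands. The article lists peak to recovery and recovery magnitude separately and does not tie the second model to either. If the outcome were a recovery-time level, the coupling would disappear. But the indices are described as delta scores, and a recovery-minus-baseline delta would share the baseline instead. The definition has to be fixed either way.

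**CORT increase may be only an adjustment.** This largely stands. The stated purpose is association between hormonal systems, which makes OXT the term of interest. A reader might infer that the model is meant to show faster recovery after a larger rise; the article does not say so. A reader might also infer that the shared peak spoils the OXT result; the simulation shows that it does not.

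**Confounding is possible, not demonstrated.** This stands. It is tempting to say that the model yields a confounded OXT effect. The article gives no hormone effect sizes, and under some patterns consistent with its hypotheses there is no bias.

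**There are partial safeguards.** The primary hormone models include group. The article also says: "Exploratory analyses will include depressive and anxiety symptomatology scores as covariates in rsFC, sMRI, and hormonal models". Symptom scores may partly stand in for group, but they are an exploratory robustness check and do nothing about a shared peak.

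**Levels bring their own built-in association.** This stands. With equal correlations of 0.3, 0.5 and 0.7 and no recovery effect, the peak term in the level model was significant in 59%, 89% and 98% of runs, through autocorrelation.

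**The VAS point is weaker.** The hypotheses name no group difference in VAS and expect none in baseline hormone levels. The article does not support calling these correlations artefacts.

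**Conclusion.** The point holds in limited form. The second regression leaves out a variable that the first includes and that the protocol's own hypotheses link to both hormones. This exposes the OXT coefficient to group confounding of uncertain sign: a false-positive rate from about 5% to about 14% under assumed shifts of up to 0.8 SD, and about 5% once group is included.

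On the natural reading of CORT recovery, the CORT-increase coefficient contains a built-in association (correlation 0.50 under equal variances and correlations, 0.20 to 0.75 in the other patterns tried) and is nearly always significant at N = 90 under the equal-correlation null. It cannot be interpreted physiologically. That problem is conditional on the definition and is separate from the OXT test.

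All group shifts and correlations are assumptions. The analysis is secondary, and the primary hormone comparisons are not affected.

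**What to change.** - State which index CORT recovery is.
- Add group to the second regression, with the sex, age and pubertal status covariates already used in the primary hormone models.
- Model recovery-level CORT on peak CORT, baseline CORT, OXT increase, group and those covariates. Alternatively, keep the delta outcome with group and covariates added, and state that the CORT-increase coefficient is not interpreted.
- In the level model, do not read the peak term as a recovery effect.
- As a lesser point, report VAS–hormone associations adjusted for group beside the bivariate correlations.

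The cost is a few sentences of analysis text. With 90 complete cases and pubertal status as one linear term, residual degrees of freedom fall from 90 − 3 = 87 to 90 − 9 = 81 in the level model. No data collection changes.

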In parallel, CORT—the end product of HPA axis activation—has been widely studied as a biomarker of stress-related psychopathology [27]. Evidence on OXT-CORT interactions is mixed: some human studies suggest that OXT buffers CORT reactivity [28, 29], while others report that higher stress-induced OXT is associated with increased CORT release and faster recovery [30]. Dysregulated post-stress CORT secretion, often observed in individuals with depressive and anxiety disorders [16, 31], has been associated with altered rsFC [32], particularly in circuits involved in emotional processing and self-regulation [33, 34]. In addition to CORT and OXT, salivary α-amylase (sAA), a marker of sympathetic nervous system activity [35], should be assessed simultaneously [36]. Altered sAA rhythms and reactivity have been observed in adolescents with depression and anxiety [37, 38], underscoring its relevance for understanding neuroendocrine dysregulation in these conditions.

However, little is known about how CORT interacts with OXT and sAA in shaping stress-induced rsFC changes. To our knowledge, no study has examined whether individual differences in OXT, CORT, and sAA reactivity predict fronto-limbic rsFC alterations following acute stress in adolescents with anxiety and depressive disorders.

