Across all analyses, effect sizes will be reported using Cohen’s d (0.2 = small, 0.5 = medium, 0.8 = large). Unless otherwise adjusted for multiple comparisons, the alpha threshold will be set at 0.05. Data will be analysed using the CONN Toolbox for neuroimaging, and IBM SPSS Statistics (Version 29.0, IBM Corp.) and jamovi (Version 2.6.22, The jamovi project, 2024) for behavioural and hormonal analyses.

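### The second OXT–CORT regression leaves out baseline CORT and group, so its OXT coefficient can be confounded, and its CORT-increase coefficient is partly built in

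*Protocol article*

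**What the plan says.** The Secondary outcomes section of the protocol article lists the predictors of both hormone regressions. For the first: "In the first model, CORT increase will be the dependent variable, with OXT increase, baseline CORT, and group as predictors". For the second: "In the second model, CORT recovery will be the dependent variable, with OXT and CORT increase as predictors". Baseline CORT and group are absent from the second list, and no reason is given.

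The second model does not say which index CORT recovery is. The Primary outcomes section offers several: areas under the curve with respect to increase and to ground, and "delta scores reflecting change from baseline to peak, peak to recovery, and recovery magnitude". The last item has no formula. It is also not explicit whether the OXT term is OXT increase (the likelier reading) or an OXT level. Values are square-root transformed before analysis.

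The scientific question comes from the Theoretical background, which calls the evidence mixed and cites studies in which "higher stress-induced OXT is associated with increased CORT release and faster recovery". The Hypotheses section expects blunted CORT and OXT responses in adolescents with depression, with or without anxiety, and no systematic group difference in baseline levels.

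**The concern.** There are two separate problems.

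- **Confounding of the OXT coefficient.** This is the coefficient of interest. Baseline CORT generally still predicts recovery once CORT increase is in the model, so any relation between OXT increase and baseline CORT leaks into the OXT estimate. Group acts in the same way, since the protocol itself expects it to shift both OXT and CORT responses. A positive OXT finding could then not be told apart from a baseline or diagnostic difference.
- **A shared sample.** CORT increase is peak minus baseline. A peak-to-recovery change contains the same peak value, and a recovery-minus-baseline score contains the same baseline value. One measurement then stands on both sides of the equation and creates an association without any physiological link.

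**Working it through.** The plan states no figure for this regression, so there is none to reproduce. The inputs from the protocol are N = 90 (30 per group), α = 0.05 and the two predictor lists. All correlations, path weights and blunting sizes below are assumptions, because the protocol gives none.

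Notation: B, P and R are CORT at baseline, peak and recovery. CORT increase is P − B.

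**1. Why baseline matters.** Suppose R = w₁P + w₂B + noise, with no OXT effect. Then

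P − R = (1 − w₁)(P − B) + (1 − w₁ − w₂)B − noise.

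Baseline keeps the weight 1 − w₁ − w₂ after CORT increase is in the model. With w₁ = 0.5 and w₂ = 0.3 this is 0.2. With w₁ = 0.4 and w₂ = 0.1 it is 0.5. It vanishes only if w₁ + w₂ = 1. Because R − B = (P − B) − (P − R), the OXT coefficient in the planned model is the same apart from sign for either delta score.

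**2. Size of the OXT bias.** Simulation at n = 90 with no true OXT effect, varying the path weights: about 7–13% false positives when OXT increase correlates 0.2 with baseline CORT, and 13–38% at 0.4. A separate set of runs with recovery = P − R and fixed correlation structures (equal variances, 1,500–2,000 runs per setting) gave these rejection rates for OXT in the planned model:

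| CORT samples | r(OXT, B) = 0 | 0.3 | 0.5 |
|---|---|---|---|
| independent | 5.4% | 22.7% | 53.0% |
| equally correlated, 0.5 | 4.1% | 11.1% | 28.5% |
| equally correlated, 0.7 | 4.5% | 9.5% | 18.9% |
| AR(1), 0.5 | 4.3% | 18.3% | 46.7% |
| AR(1), 0.7 | 5.5% | 16.1% | 36.3% |
| AR(1), 0.9 | 4.5% | 8.0% | 17.9% |

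With baseline CORT added, every cell returns to about 4–6%.

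**3. Group.** Here both clinical groups have OXT and peak CORT lowered by 0.5 or 0.8 SD (assumed). False positives for OXT:

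| CORT samples | Blunting | r(OXT, B) | As planned | + baseline | + group | + both |
|---|---|---|---|---|---|---|
| equal, 0.5 | 0.5 | 0 | 6.2% | 5.6% | 5.2% | 5.2% |
| equal, 0.5 | 0.5 | 0.3 | 19.8% | 6.4% | 12.9% | 5.5% |
| equal, 0.5 | 0.8 | 0 | 9.1% | 6.0% | 5.0% | 4.4% |
| equal, 0.5 | 0.8 | 0.3 | 31.0% | 7.3% | 12.5% | 5.1% |
| AR(1), 0.7 | 0.5 | 0 | 8.0% | 7.0% | 5.0% | 4.6% |
| AR(1), 0.7 | 0.5 | 0.3 | 30.5% | 7.0% | 15.2% | 4.6% |
| AR(1), 0.7 | 0.8 | 0 | 17.2% | 14.2% | 5.3% | 4.4% |
| AR(1), 0.7 | 0.8 | 0.3 | 52.7% | 14.9% | 14.8% | 5.0% |

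Only the model with both covariates holds about 5% throughout.

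**4. The shared sample.** With equal variances,

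corr(P − R, P − B) = (1 − r_PB − r_PR + r_BR) / (2√[(1 − r_PB)(1 − r_PR)]).

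- Equally correlated samples (all r): (1 − r)/(2(1 − r)) = 0.50 at any r. CORT increase is significant in 99.9–100% of runs.
- Serial decay (r, r, r²): (1 − r)²/(2(1 − r)) = (1 − r)/2. For r = 0.5, 0.7 and 0.9 this is 0.25, 0.15 and 0.05, with significance in 68%, 28% and 8% of runs.
- Recovery as R − B: simulated correlation 0.49–0.69, significance 99–100% in all structures.
- Recovery as the level R: no sample is shared. Significance is about 5% for independent or equally correlated samples when OXT is unrelated to baseline.

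Adding baseline does not remove the coupling for P − R. By step 1 the CORT-increase coefficient is then 1 − w₁, which is zero only if recovery follows peak one for one.

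**The case against.** The strongest reply is that the recovery index is not fixed, and an article may leave its formula to a fuller document. If recovery means the recovery-sample level, nothing is shared. A change from peak to recovery may also be scored R − P, which reverses the sign of the association. CORT increase may be only an adjustment variable, since no stated hypothesis concerns its coefficient. The OXT bias needs a correlation with baseline CORT that the protocol does not report; without it, and without a group effect, the OXT test keeps its size (4–6%). The analysis is secondary.

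Most of this stands and limits the point. A reader might infer that CORT increase must come out significant whatever the biology. The documents do not support that: under serial decay the rate for peak-to-recovery change falls as low as 8%, and the index is not stated. A reader might also infer that the OXT result will be false. That does not follow either, because the inflation is conditional on assumed correlations.

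The omission itself is not answered. The article gives the predictor list for the second model and leaves out two variables that it uses one sentence earlier. Reading recovery as a level does not escape baseline confounding: at r = 0.3, OXT false positives for that outcome ranged from 5% (independent samples) to 71% (AR(1) 0.9). Group confounding does not depend on a correlation between OXT and baseline, and the protocol's own hypotheses motivate it.

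**Conclusion.** The point holds as a minor one. As listed, the second regression can confound the OXT coefficient with baseline CORT and with group. The size depends on assumptions: about 7–13% false positives at a correlation of 0.2 between OXT increase and baseline CORT, 13–38% at 0.4, and no inflation if they are unrelated and group plays no part. Assumed group blunting of 0.5–0.8 SD raises the rate to 6–17% with no baseline correlation and to 20–53% with a correlation of 0.3.

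Under the delta-score readings, the association of CORT recovery with CORT increase is partly built in. The correlation is 0.50 for exchangeable samples, and weaker for peak-to-recovery change if correlation decays over time. This is enough to bar a physiological reading of that coefficient, but not enough to call its significance guaranteed. Neither primary outcome is affected.

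**What to change.** State which recovery index and which OXT term are meant. Then replace the second model with recovery-sample CORT (square-root scale) regressed on peak CORT, baseline CORT, OXT increase and group. Interpret only the OXT coefficient. Do not interpret the coefficient of CORT increase, or of peak CORT in its place, as evidence of a link between reactivity and recovery.

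With peak and baseline both in the model, the OXT coefficient is the same apart from sign whether the outcome is R, P − R or R − B, so the choice among these no longer affects the OXT result.

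The cost is a line of wording and three degrees of freedom. At N = 90 the planned model has 90 − 3 = 87 residual degrees of freedom. The replacement has an intercept, peak, baseline, OXT and two group terms, so 90 − 6 = 84. The saliva data are the same.

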### Expense allowance

Adolescents participating in our study receive a gift voucher of €50 as an expense allowance for participation.

### Adverse event reporting and harms

No adverse events are expected from study participation, and medically necessary treatments will not be delayed or altered. In the event of significant symptom worsening, therapeutic support will be offered. Participation is voluntary, and both adolescents and their legal guardians may withdraw at any time without providing a reason.

